**Figure 1 F1:**
[figure not shown]
Flow chart of trial recruitment and follow-up in the APRIL Trial.

**Figure 2 F2:**
[figure not shown]
Schedule of trial activities in the APRIL Trial. ■ Liver function test (LFT) – if the blood test has been already conducted as part of standard of care within the past 3 months then it can be used and there is no need to repeat further test unless clinically indicated. Follow-up blood tests to be done within 7 days of target date. □ Urine pregnancy test for women of child-bearing potential (WOCBP) – urine pregnancy test will be done at screening, after completing month 1 and month 2 trial treatment and at the end of the treatment to confirm nil pregnancy. If a female subject becomes pregnant during the treatment period, she should immediately notify the investigator and trial medication should be permanently discontinued. ● Monthly outcome questionnaires to be completed within 2 weeks of completion of month 1, month 2 and month 3 treatment. ○ Randomisation must be completed within 2 weeks of confirmation and signing of participant eligibility. § To post month 2 and month 3 trial medication along with the trial medication diary a week prior the start of cycle. * To start treatment within 7 days of randomisation.

### Sample size {14}

Published data from an online survey of long covid patients’ grade distribution on the PCFS (4 [severe] to 0 [none]) improved from 3.4%, 49.4%, 35.1%, 7.1% and 5.0% at 3 months to 2.1%, 43.9%, 35.1%, 10.5% and 8.4% at 6 months, respectively.^29^ If Ashwagandha can improve symptoms to a similar extent at 3 months, this translates to an overall OR of 0.71 on the ordinal logistic regression analysis (with an OR <1 indicating a shift to a lower grade of symptoms). To improve symptoms with a more modest OR of 0.75, a sample size of 2500 gives in excess of 90% power (or 80% power to detect an even more conservative OR of 0.80). An OR of 0.75 would result in the percentages in each grade (grades 4 to 0) being 2.6%, 43.1%, 38.8%, 9.0% and 6.6% in the Ashwagandha arm at 3 months. The primary analysis will include an adjustment for the baseline value of the primary outcome scale, which is expected to increase the power further. These calculations are designed to be robust to limited anticipated loss to follow-up (given the relatively short-term and non-onerous nature of the trial).

### Recruitment {15}

Participants will be recruited by a clinical investigator based at the trial’s participating sites. Trial site teams will search their local patient databases for potentially eligible individuals and contact them by letter or in person to invite them to join the trial.

New study sites will be recruited by the trial coordinating centre (LSHTM) through letters of invitation or personal communications and networks, as appropriate.

### Assignment of interventions: allocation

#### Sequence generation {16A}

Participants will be randomised online in a 1:1 ratio to the intervention or control arms. A randomisation list will be generated by the independent trial statistician, which will include a list of randomisation IDs and their corresponding trial allocation, using randomly permuted blocks with random block sizes to ensure balance throughout the recruitment period.

#### Concealment mechanism {16B}

The randomisation list will be used by an independent labelling partner at a GMP facility in the UK (IMP Pharmaceuticals Ltd) to apply blinded labels to all the bottles. The blinded bottles will be sent to the trial coordinating centre (in random order) to be dispatched to participants according to their assigned randomisation ID. None of the staff involved in running the study will have access to the unblinded randomisation lists. Neither participants nor any staff involved in running the trial will be made aware of the participant’s randomisation status.

#### Implementation {16C}

Described above.

## Assignment of interventions: blinding

### Who will be blinded? {17a}

Participants; study staff conducting the recruitment, handling participant communications and collecting outcome information; and study investigators and analysts will all be blinded to the participant’s assignment status. Only the independent unblinded staff member (responsible for generating the randomisation lists and the unblinded statistical reports to the data monitoring committee [DMC]), and the independent labelling partner (not otherwise involved in the study) will be aware of the assignment of interventions. The DMC will be unblinded for SAE monitoring and can also request unblinded interim analyses of outcomes (to be prepared by the independent unblinded statistician).

### Procedure for unblinding if needed {17b}

In general, there should be no requirement for unblinding of the allocated treatment in this trial. If a participant wishes to withdraw, or a new contraindication to Ashwagandha arises, a withdrawal process will be followed (but unblinding will not occur). In exceptional circumstances, the study investigator responsible for a particular participant may need to unblind that participant (eg, in a clinical emergency where clinical management requires knowledge of which treatment the participant has received). In the case of such eventualities, all study investigators will have access to unrestricted and immediate access to break the treatment code via a password-protected online system that allows them access to only the requested participant’s treatment code. The responsibility to break the treatment code in emergency situations resides solely with the investigator. An electronic logging system will be in place to alert the trial team to all occurrences of unblinding of an investigator so that this can be logged and followed up appropriately.

### Data collection and management

#### Plans for assessment and collection of outcomes {18A}

Follow-up for primary and secondary outcomes will be through a brief monthly online or postal survey. All questionnaire instruments are previously validated (full versions available in the appendix). Questionnaires will be sent monthly for 3 months (ie, end of months 1, 2 and 3). To be valid, completed questionnaires should be received within 2 weeks of the target completion date (but ideally as close to the target date as possible). Automated email or text reminders will be sent as per participant preference. In case participants are unable or unwilling to complete surveys online, paper questionnaires in pre-paid return envelopes will be posted each month along with the supplement/placebo packages.

The study doctor’s team will assess all participants at least monthly and conduct symptom-guided assessment as described in NICE Long Covid guidelines. Assessments will take place at the end of 30 ± 3 days (first interim assessment), 60 ± 3 days (second interim assessment) and 91 (to 98) days (final end of trial assessment) from treatment initiation. At each assessment, they will actively elicit the participant’s history related to a) any worsening of their long covid, b) exacerbation of any other pre-existing conditions and c) any side effects that might be related to the drug (including AE/SAE assessment if applicable). To guide assessment of c), we will provide the clinical teams with a list of possible side effects that have been observed previously for this trial product (regardless of whether causally attributed). Monthly assessments could be conducted remotely or in-person, based on requirements (eg, if blood tests are required). Following the initial assessment, further in-person follow-up, including any indicated tests and investigations, will be sought if needed based on the participant’s symptom assessment and as guided by relevant local and national guidelines. In addition to these monthly clinical assessments, LFTs (AST, ALT and bilirubin) will be conducted at 30 (ie, along with first interim clinical monitoring assessment) and 91 (ie, at the end of trial assessment) days. The test at 30 days is intended to check for any early acute liver toxicity associated with the trial medication; if there is any abnormality noted, participants will be assessed on-site. The test at 91 days must be performed at least 24 hours after the last dose of the trial medication and is intended to assess for any longer-term effects associated with the cumulative build-up of the product in the system. All WOCBP will have to complete a urine pregnancy test monthly during the trial. These tests will be done after completing month 1 and 2 trial treatments and after completing month 3 treatment at the end-of-study assessment to confirm that no pregnancies occurred during the trial treatment phase. The tests will be posted directly to the women and may be done at home or at the participant’s trial site. All clinical and laboratory measures will be made as per the trial site’s standard NHS clinical protocols to ensure that the assessment of these safety outcomes complies with local clinical standards.

### Plans to promote participant retention and complete follow-up {18B}

Automated email or text reminders will be sent as per participant preference. If participants fail to respond for 2 months in a row, follow-up calls will be made to them (no more than three times) to ascertain their participation status in the trial (including vital status). If participants are withdrawn from the treatment (eg, at their own request or as recommended by their study investigator), we will give them the option to continue completing the online follow-up questionnaires if they wish (referred to as ‘partial withdrawal’).

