### Criteria for discontinuing or modifying allocated interventions {11B}

Participants will be required to immediately discontinue the trial treatment if any of the following criteria are met:

Any serious AE (SAE, defined as a life-threatening illness, hospitalisation or onset of major disability) considered related to the study IMP.Any grade ≥3 (severe) or more severe AEs considered related to the study IMP.Pregnancy.Any medical condition that may jeopardise the participant’s safety if he or she continues study treatment.Use of prohibited medication as per the eligibility criteria.Liver toxicity:Alanine transaminase (ALT) or AST >8× ULN.ALT or AST >5× ULN for more than 2 weeks.ALT or AST >3× ULN and (TBL >2× ULN or international normalised ratio >1.5).ALT or AST >3× ULN with the appearance of fatigue, nausea, vomiting, right upper quadrant pain or tenderness, fever, rash and/or eosinophilia (>5%).

There are no planned intervention modifications in this trial.

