### Participant timeline {13}

Each participant will take part in the trial for 3–4 months (depending on the time taken in the pre-treatment stage). A flowchart of trial recruitment and follow-up is given in figure 1, and the detailed schedule of trial activities is given in figure 2. In summary, participants will provide consent and undergo eligibility screening (including clinical assessment, medical history, baseline LFT and urine pregnancy test for WOCBP) with their study doctor. Once confirmed as eligible, they will be sent an online questionnaire to complete (baseline questionnaire). They will be electronically randomised into the trial once the questionnaire is completed. They will be sent their trial medication by post as soon as possible after randomisation and contacted to confirm receipt and the day of medication initiation (day 0). After 30 days of taking the trial medication, they will have received their second pack of trial medication by post and an online questionnaire to complete and will meet with their study doctor’s team for clinical monitoring (including month 1 LFT) (±3 day window). After 60 days of taking the trial medication, they will have received their third pack of trial medication and a link to their online questionnaire to complete and will have a clinical monitoring assessment with their study doctor’s team (±3 day window). After 91 days, participants will complete their final online questionnaire and clinical monitoring assessment with their study doctor (including month 3 LFT) (+7 day window) and be discharged from the trial (unless any clinical concerns have arisen, which might indicate further clinical monitoring). WOCBP will additionally undergo urine pregnancy tests at each monthly monitoring assessment to confirm that they are not pregnant while on trial medication (for which month 1 and 2 monitoring assessments may be done at home and reported to the study doctor’s team).

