### Methods in analysis to handle protocol non-adherence and any statistical methods to handle missing data {20C}

For all primary and secondary analyses, treatment allocation will be assumed to be ‘as randomised’ (intention-to-treat). An exploratory per-protocol analysis may also be conducted for comparison purposes. Multiple imputations will be used to handle missing data.

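### The protocol does not secure month-3 PCFSS data for everyone randomised, so its intention-to-treat estimate leans on an imputation assumption that the article does not state

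*Protocol article*

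**What the plan says.** The statistical methods section (20A) and the section on non-adherence and missing data (20C) of the protocol article specify an intention-to-treat analysis by randomised allocation. On missing data, 20C adds only: "Multiple imputations will be used to handle missing data".

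Five collection rules bear on whether the month-3 PCFSS exists for everyone randomised:

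- **After stopping treatment** (18B): "we will give them the option to continue completing the online follow-up questionnaires if they wish". The article calls this partial withdrawal. Section 11B makes some stopping compulsory: "Participants will be required to immediately discontinue the trial treatment if any of the following criteria are met". The criteria include related serious or severe adverse events, liver toxicity, pregnancy and use of prohibited medicines.
- **Time origin** (Participant timeline, 13): randomisation comes before dispatch of the tablets, and participants are then "contacted to confirm receipt and the day of medication initiation (day 0".
- **Questionnaire timing** (Figure 2 legend): "Monthly outcome questionnaires to be completed within 2 weeks of completion of month 1, month 2 and month 3 treatment". Section 18A adds a validity rule: "completed questionnaires should be received within 2 weeks of the target completion date".
- **Paper route** (18A): "paper questionnaires in pre-paid return envelopes will be posted each month along with the supplement/placebo packages".
- **Non-response** (18B): "If participants fail to respond for 2 months in a row, follow-up calls will be made to them", at most three times, to find out whether the person is still taking part.

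**The concern.** An intention-to-treat estimate needs the outcome of people who stopped or never started, on the same calendar as everyone else. Here those are the people whose outcome is least likely to be collected. Continuing is an offer, the clock is defined by taking tablets, and the paper form shares a parcel with medication that a stopper may no longer be sent. Several compulsory stopping criteria are drug-related, so the resulting gaps could differ between arms.

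If few stoppers are followed, any imputation has little information on how stoppers fare. The estimate then depends on an assumption instead of data. An imputation model that ignores stopping would move it towards the effect in people who stayed on tablets.

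**Working it through.** **Step 1. The plan's own figures.** Inputs from Sample size (14): grades 4 to 0 in the control arm 3.4, 49.4, 35.1, 7.1, 5.0%; N = 2500; 1:1 allocation. Two-sided alpha of 0.05 is my assumption, as the article states none. A proportional-odds fit of the two survey distributions gives OR 0.710 (stated 0.71). Whitehead's formula is

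power = Φ( √[N/12 · (1 − Σp̄³)] · |ln OR| − 1.96 ).

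At OR 0.80 the active grades are 2.74, 44.49, 38.09, 8.51, 6.17%. Then Σp̄³ = 0.153, √(208.3 × 0.847) = 13.28, and 13.28 × 0.2231 − 1.96 = 1.00, which gives 84.2%. With 10% loss (N = 2250) it is 80.3%. At OR 0.75 power is 96.9%. The stated powers (80% at 0.80, above 90% at 0.75) hold, so the sample size is not in error here.

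**Step 2. When the calls come.** Targets are days 30, 60 and 91, each with 2 weeks' grace, so the windows close on days 44, 74 and 105. I count a month as missed when its window closes.

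- Months 1 and 2 missed: the call falls after day 74, in time for month 3.
- Months 2 and 3 missed: the second miss is known at day 105, when the month-3 window has closed.
- Only month 3 missed: the rule is never triggered.

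**Step 3. People without a clock.** A randomised person who confirms no first tablet has no day 0, hence no day 91 in the article. For someone who stops in week 3, completion of month-3 treatment, the event that the Figure 2 legend counts from, does not occur.

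**Step 4. Size, by assumption.** The document gives no stopping rates. Let a share f stop in each arm. Stoppers in both arms have the control distribution shifted worse by OR w, with no drug effect. The rest of the active arm has on-treatment OR 0.80. Each arm is then (1 − f) × stayers + f × stoppers, and a proportional-odds model is fitted, unadjusted for baseline.

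Hand check at the grade 3–4 cut, f = 10% v 5%:

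- w = 1: active 0.9 × 47.23 + 0.1 × 52.80 = 47.78%, control 52.80%; (47.78/52.22)/(52.80/47.20) = 0.818.
- w = 2: stoppers have 69.11% in grades 3–4, active 49.42%, control 53.62%; (49.42/50.58)/(53.62/46.38) = 0.845. The fit over all cuts gives 0.844.

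Suppose imputation ignores stopping and a share q of stoppers is followed. The imputed arm then looks like those observed, with stoppers weighted fq/(1 − f + fq). For q = ½ that is 0.05/0.95 = 5.3% (active) and 0.025/0.975 = 2.6% (placebo).

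| Stopping (active v placebo) | w | True ITT OR | Estimated, none followed | Estimated, half followed |
|---|---|---|---|---|
| 10% v 5% | 1 | 0.818 | 0.800 | 0.809 |
| 10% v 5% | 1.5 | 0.834 | 0.800 | 0.818 |
| 10% v 5% | 2 | 0.844 | 0.800 | 0.823 |
| 20% v 10% | 1 | 0.836 | 0.800 | 0.820 |
| 20% v 10% | 2 | 0.89 | 0.800 | 0.851 |

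**Step 5. Direction.** With no drug effect and w = 1, the true and estimated ORs are both 1.00. With no drug effect, 20% v 10% stopping and w = 2, the true OR is 1.07 against 1.00 estimated if none are followed. If stoppers do better (w = 1/1.5), it is 0.96 against 1.00, the other way. With a drug effect, unequal stopping is not required: 10% in both arms still gives a true OR of about 0.82 against 0.80.

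**The case against.** The strongest reply is that nothing in the article says stoppers are imputed as though still on treatment. Section 20C names multiple imputation and no model, and the statistical analysis plan, which is not shown, may include treatment status. That stands. A reader might infer from these rules that stoppers and non-starters will be imputed as on-treatment, contrary to intention-to-treat. The documents do not support this: allocation is analysed as randomised, and stoppers who accept partial withdrawal have observed outcomes that need no imputation.

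It can also be said that questionnaires are always voluntary, that postal forms exist for those who prefer them, that the eligibility and data management sections mention telephone completion, and that the latter allows phone contact when much data is missing. The modes therefore largely exist. What remains is that the article ties none of them to participants who have stopped: partial withdrawal names online questionnaires, and paper forms go with the medication packages.

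A default date for non-starters may be in the full protocol, and such people may be few. But the article does state its time origin, and that origin does not cover them.

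Finally, the illustration stacks assumptions. Following half of the stoppers roughly halves the gap, and month-1 and month-2 scores could help an imputation model further. A general claim that the rules favour the arm with more stopping would also be wrong, as Step 5 shows.

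**Conclusion.** The point holds as a weakness of data collection. Four stated rules (opt-in follow-up after stopping, a clock tied to taking tablets, paper forms sent with medication, and calls that can come after the month-3 window) leave the month-3 PCFSS unsecured for stoppers and never-starters. An analysis plan cannot recover outcomes that were not collected. The intention-to-treat estimate is put at risk and rests on an unstated imputation assumption; it is not contradicted.

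With 10% v 5% stopping, on-treatment OR 0.80, no effect after stopping, stoppers no better than others (w = 1 to 2) and imputation that ignores stopping, the gap is about 0.02 to 0.04 on the OR scale if no stopper is followed, and about 0.01 to 0.02 if half are. Doubling the stopping rates widens it to about 0.04 to 0.09 with none followed. All these rates are assumptions. The gap can vanish or reverse if stoppers fare the same or better.

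**What to change.** In the protocol:

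- Make outcome collection by online, postal or telephone form the default after treatment stops, ended only by explicit withdrawal from follow-up.
- Post paper forms independently of medication.
- When a month-3 form is missed, attempt to collect the PCFSS itself, without waiting for a second missed month.
- Give participants with no confirmed start a default outcome date counted from randomisation, for example by using the 7-day start window in the Figure 2 legend.

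Separately, confirm that the imputation model in the statistical analysis plan accounts for treatment discontinuation.

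The cost is an amendment to the wording and a few more questionnaires and contacts. Participants keep the right to leave follow-up, and no treatment rule changes. The Trial status section has recruitment running to July 2026 and already foresees amendments, so the change could still benefit later participants.

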### Data management {19}

Completed informed consent forms will be retained by clinical trial sites as per their standard procedures. Data from screening, registration and follow-up case report forms will be stored on secure servers within the trial coordinating centre’s secure data centre. These data systems will be access-controlled with access only provided to necessary study staff such as those entering and monitoring the data, and trial staff based at study sites will only be able to view information pertaining to participants from their site. Any paper-based case report forms will be stored in locked cabinets at the trial coordinating centre. Where data entry is required (ie, for any sections completed by post or telephone), entry into the same database (via Redcap forms) will be overseen and checked by the trial manager. The database will be developed in a way that flags up unusual data values, allowing participants to be contacted by the trial team via phone if there are large amounts of unusual/missing data. Once the trial data entry is completed and all data queries have been satisfactorily resolved, the database will be locked down by the trial manager by revoking site staffs’ access and downloading the final version of the database as an un-editable file stored on the sponsor’s secure servers. Data and all appropriate documentation will be stored for a minimum of 10 years after the completion of the study, including the follow-up period.

### Confidentiality {27}

All personal information about potential and enrolled participants will be stored securely at the trial sites or trial coordinating centre in accordance with general data protection regulations and following stringent confidentiality guidelines. It will only be accessible to necessary study personnel on a need-to-know basis (eg, for conducting participant follow-up and posting trial medications), following relevant consents from participants. Only de-identified data required for conducting trial analyses will be shared with the study analysts. These data extracts will be de-identified because no participant identifiers (eg, name and date of birth) will be included, and participants’ trial IDs will be replaced with new random IDs. They will be extracted from the main locked study database by the trial manager and shared with the statistical analyst via shared folders within the sponsor’s secure servers. Data handling will be in accordance with standards set out in the UK NHS Data Security and Protection Toolkit.

